### Procedure

Study procedures will be carried out in the following steps:

Once a patient meets inclusion criteria and provides a written informed consent, the following data will be collected: age, sex, weight, height, BMI, smoking history, type and duration of surgery, comorbidities, arterial blood gas analysis (PH, PaO_2_, PaCO_2_, FiO_2_), chest X-ray or computed tomography (CT), pain (11-point NRS), and the time from admission to the ICU to the first mobilization.The following baseline parameters will be recorded when the patient is in decubitus position (T_0_): heart rate (HR), blood pressure (BP), oxygen saturation (SO_2_), respiratory rate (RR), and EIT ROI 1-4. The duration of each EIT recording will be 2 min.The patient will be seated in a chair beside the bed with assistance. Oxygen therapy method and oxygen concentration will be the same as that before getting out of bed.The parameters presented in step 2 will be recorded at 15 min (T_1_), 30 min (T_2_), 60 min (T_3_), 90 min (T_4_), and 120 min (T_5_) for each patient after getting out of the bed.

After patients reach the 120-min time point, their participation in the study will be complete. No further interaction with the enrolled patients is planned.

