### Outcome Measures

The primary outcomes include the improvement in homogeneity of pulmonary ventilation distribution after mobilization and optimal duration of early mobilization. Secondary outcomes include optimal duration of early mobilization for different surgical methods; correlation between bed rest time and optimal duration of early mobilization; and correlation between blood oxygen saturation, oxygenation index, and improvement in homogeneity of pulmonary ventilation distribution.

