### Definitions

Homogeneity index is defined as the ratio of EIT values of ventral to those of dorsal ROIs; thus, lower levels (~1.0) represent better homogeneity of ventilation (18).Optimal duration of early mobilization is defined as the mobilization time at which homogeneity index is closest to 1.Bed rest time is the time from the start of surgery to the time of first mobilization.

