### Statistical Analysis

A prior study that used EIT to assess ventilation distribution in patients undergoing major open abdominal surgery found that a two-sided significance level (α) of 0.05 and a target power of 80% would require 10 subjects (19). We aim to recruit 50 patients, surpassing the minimum necessary for our target power and significance level. Analyses will be conducted using SPSS 21.0 (IBM, Armonk, New York, USA). Continuous variables will be expressed as means (95% confidence intervals, CI) or as medians (interquartile range). Categorical variables will be analyzed using the chi-square test. Means or medians will be compared between groups using the *t*-test, the Mann-Whitney *U*-test, and one-way analysis of variance with F- or Kruskall-Wallis tests, when appropriate. Pearson correlation or Spearman rank correlation coefficient will be used to assess the correlation between variables, as appropriate. Intention-to-treat analyses will be carried out using mixed models. All tests will be 2-sided, and significance will be set at the 0.05 probability level.

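### The primary outcome of optimal duration always names a time: if the seated readings do not differ, the per-patient pick is random and averages 63 minutes

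*Protocol article*

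**What the plan says.** Outcome Measures gives the outcome primary status: "The primary outcomes include the improvement in homogeneity of pulmonary ventilation distribution after mobilization and optimal duration of early mobilization". Definitions sets the measure, "Homogeneity index is defined as the ratio of EIT values of ventral to those of dorsal ROIs", with values near 1 as the target, and then the selection rule: "Optimal duration of early mobilization is defined as the mobilization time at which homogeneity index is closest to 1".

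Procedure supplies the candidate times. After a baseline in bed (T0), the parameters are "recorded at 15 min (T_1_), 30 min (T_2_), 60 min (T_3_), 90 min (T_4_), and 120 min (T_5_) for each patient", and "The duration of each EIT recording will be 2 min". No replicate recording at a time point is described.

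Two secondary outcomes reuse the result: optimal duration by surgical method, and the "correlation between bed rest time and optimal duration of early mobilization". Bed rest time is a patient-level quantity in Definitions, so this correlation needs one optimal duration per patient. For the primary outcome, Definitions does not say whether the time is picked per patient or from the cohort curve.

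Statistical Analysis lists two-group and multi-group comparisons, correlations and mixed models. It ties none of them to optimal duration.

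**The concern.** The rule selects the best of five readings. It has no tolerance, no provision for a flat time course and no condition that the chosen time beat another. T0 is recorded in bed and so is not naturally a mobilization time. The rule therefore cannot return the answer that no duration is preferred.

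The article wants the result as a basis for personalized mobilization plans. Two opposite situations leave the five seated readings flat: sitting changes nothing, or sitting gives its whole benefit within 15 minutes. The rule reports the same thing in both. A figure near one hour is clinically plausible and could be read as a finding when it reflects only the spacing of the measurement times.

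**Working it through.** **The plan's own figure.** The only design figure is a minimum of 10 subjects, from a prior EIT study (two-sided 0.05, 80% power). No effect size or SD is given, so it cannot be reproduced. Back-solving with the normal approximation gives a standardized paired effect of (1.96 + 0.84)/√10 = 0.89. This has no bearing on choosing among times. The article states no figure for optimal duration.

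**Inputs from the article.** Candidate times 15, 30, 60, 90 and 120 min; one 2-minute recording at each; 50 patients planned.

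**Flat course, per-patient pick.** Assume equal true values at T1 to T5 and exchangeable errors. Each time then has probability 1/5 of lying closest to 1, whatever the size of the error.
- Mean = (15 + 30 + 60 + 90 + 120)/5 = 315/5 = 63 min.
- Variance = (48² + 33² + 3² + 27² + 57²)/5 = 7380/5 = 1476, so SD = 38.4 min.
- With 50 patients, SE = 38.4/√50 = 5.43. The 95% half-width is 2.01 × 5.43 = 10.9 min, giving about 52 to 74 min.
- In simulation (4,000 trials of 50 patients) the trial median was exactly 60 min in about 80% of trials.
- With errors autocorrelated over time (assumed decay 30 or 120 min), the mean was 65 to 66 min, 95% range about 54 to 78, and the median was exactly 60 in 67 to 76% of trials.

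**Flat course, pick from the cohort mean curve.** Each time won in about 20% of trials (about 15 to 27% with autocorrelation). Here 60 min is not favoured; the answer is close to a random draw.

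**Real trends.** The article gives no repeatability for the index, so these are assumptions shown over a range: log-normal index, between-patient SD 0.2 and within-patient SD 0.05, 0.1 or 0.2 on the log scale, independent errors.

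| True course of the index | Mean per-patient pick (min) at SD 0.05 / 0.1 / 0.2 | Cohort curve picks the true best time |
|---|---|---|
| Falls from 1.5 at 15 min to 1.1 at 120 min | 104 / 96 / 82 | 100% / 100% / 98% |
| Falls from 1.5 to 1.3 | 102 / 87 / 74 | 100% / 98% / 83% |
| Falls from 1.5 to 1.4 | 88 / 76 / 69 | 98% / 82% / 60% |
| Best at 30 min by 0.1 log units | 35 / 46 / 55 | 100% / 93% / 75% |

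A course that is best at 15 min and then worsens gave 29, 37 and 48 min. A true optimum at 60 min gave 60, 60 and 61 min, almost the flat-course value. The depth of these two courses is a further assumption, so only their direction matters here.

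**The case against.** **The outcome does respond to duration.** A reader might infer that it comes out at about an hour under any true time course. The table contradicts that: per-patient means ran from 29 to 104 min when duration mattered. Only a weak effect with large noise stays near the flat-course value; the fall from 1.5 to 1.4 at SD 0.2 gave 69 min, inside 52 to 74. This objection stands and limits the point to flat or nearly flat courses.

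**The level of the pick is not stated.** On the cohort curve a strong trend is found reliably. True, but a flat course then returns a near-random time, which is no better, and the bed-rest correlation needs per-patient picks in any case.

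**Other parts of the plan help.** The abstract compares each time point with baseline, mixed models are planned, and the other primary outcome could separate no benefit from immediate benefit. The spread of picks over the five times would also look different under a true 60-minute optimum. None of this is attached to the definition, which names a time regardless.

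**Two further inferences are not supported.** One is that patients who return to bed early would bias the pick. The article plans all five readings for each patient and describes no early return: "After patients reach the 120-min time point, their participation in the study will be complete". The other is that the trial will test the best of five readings against baseline and so declare a spurious gain. No such test is planned.

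**Conclusion.** The point holds for a flat course from 15 to 120 min. Followed exactly, the rule then still reports an optimum: on average 63 min per patient (95% CI about 52 to 74 with 50 patients; 65 to 66 min with autocorrelated errors), or a near-random time from the cohort curve. A mean or median near 60 min cannot be distinguished from no duration effect, and the two secondary outcomes inherit the problem. The 63-minute figure rests on exchangeable errors and on T0 not being a candidate, not on how large the errors are. How far a real trend would move the result depends on the repeatability of the index, which is unknown here, so it cannot be said that the picks are mostly noise. Because this is a primary outcome fixed in the article's own definition, it should be corrected before the data are analysed.

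**What to change.** Replace the pick with a time profile estimated from recordings already planned.

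1. Analyse distance from balance, |ln(ventral/dorsal)|, in one repeated-measures mixed model with T0 to T5 as a categorical factor. The absolute log ratio treats ventral and dorsal excess alike, so patients on opposite sides of 1 do not cancel.
2. Report the mean and 95% CI at each time, each seated time against T0, and the differences among T1 to T5.
3. Name an optimal duration only if the time effect over T1 to T5 is shown and the chosen time improves on T0. Take it from the cohort profile, with a patient-level bootstrap interval. Otherwise conclude that no duration between 15 and 120 min is preferred.
4. Replace the two secondary analyses of the per-patient pick with surgery-type × time and bed-rest-time × time terms in the same model.

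**Cost.** No new data are needed, and Study Status says recruitment was still in preparation. The trial may have to report that no single optimum can be identified. The change redefines a primary outcome and replaces two secondary analyses, so under Ethics and Dissemination it must be notified to the review board and the registry.

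### The closest-to-1 rule scores a patient still improving at the last reading as optimal at 120 min, so the primary outcome can report the end of measurement as the optimum

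*Protocol article*

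**What the plan says.** The Definitions section sets the index and the rule. "Homogeneity index is defined as the ratio of EIT values of ventral to those of dorsal ROIs", with values near 1 taken as better homogeneity. Then: "Optimal duration of early mobilization is defined as the mobilization time at which homogeneity index is closest to 1".

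The Procedure section sets the times at which the index is seen after the patient leaves bed: 15, 30 and 60 min, then "90 min (T_4_), and 120 min (T_5_) for each patient after getting out of the bed". It closes the window explicitly: "After patients reach the 120-min time point, their participation in the study will be complete", and "No further interaction with the enrolled patients is planned".

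The Outcome Measures section gives the quantity its weight: "The primary outcomes include the improvement in homogeneity of pulmonary ventilation distribution after mobilization and optimal duration of early mobilization". Two secondary outcomes also rest on it: "optimal duration of early mobilization for different surgical methods", and its correlation with bed rest time.

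The Statistical Analysis section lists means or medians, the t-test, Mann-Whitney, one-way ANOVA or Kruskal-Wallis, Pearson or Spearman, each as appropriate, and mixed models for the intention-to-treat analyses. It assigns none of these to the optimal duration. The Strengths and Limitations section mentions the single centre and the single lung slice, but not the 120-minute limit.

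**The concern.** The rule asks only which time is closest to 1. It does not require the index to have reached 1, levelled off or turned back, and it has no category for an optimum later than the last reading. If a patient's index is still approaching 1 at T5, the closest reading is T5 by construction, wherever the window happens to end. The recorded 120 min then means that the best point was not seen, but it enters the data looking like an observed optimum.

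Three outcomes are exposed: one primary and two secondary. The Background section says the time-course results are to provide a basis for personalized mobilization plans, so a headline duration that only reflects the length of the session would be read as more than it is. In the secondary analyses, a mean, t-test, ANOVA or Pearson coefficient would take these ceiling values as exact minutes.

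**Working it through.** The plan gives no figure for this outcome (no expected time course, SD or share at each time), so there is nothing of its own to reproduce. The check applies the rule as written.

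**Inputs from the protocol.** Candidate times t = 15, 30, 60, 90, 120 min (Procedure). Assigned optimum = the t with the smallest distance of the index from 1 (Definitions). That the choice is made among the readings is an inference, but the index is measured only then and no interpolation is described.

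**Step 1: the mechanism, without noise.** Take an assumed index 1 + 0.6 × 2^(−t/h).

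| h (min) | Index at 90 min | Index at 120 min | Assigned optimum |
|---|---|---|---|
| 20 | 1.027 | 1.009 | 120 min |
| 40 | 1.126 | 1.075 | 120 min |
| 80 | 1.275 | 1.212 | 120 min |

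A patient who has practically arrived at 1 and one who is still well short of it receive the same value.

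**Step 2: how many patients could be affected.** All of the following are assumptions: log index = 0.7 × exp(−t/τ) + N(0, s), so the starting ratio is exp(0.7) ≈ 2.01. There are 200,000 simulated patients per scenario, and the optimum is the time with the smallest absolute log index. Share assigned 120 min:

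| τ (min) | s = 0.05 | s = 0.1 | s = 0.2 |
|---|---|---|---|
| 5 | 21% | 20% | 20% |
| 10 | 26% | 24% | 21% |
| 15 | 32% | 28% | 23% |
| 30 | 51% | 39% | 30% |
| 60 | 81% | 61% | 41% |
| 120 | 85% | 65% | 46% |
| 240 | 77% | 56% | 39% |
| flat | 20% | 20% | 20% |

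The flat course gives 1/5 = 20% by chance alone, with mean assigned optimum (15 + 30 + 60 + 90 + 120)/5 = 63 min.

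At τ = 240 the true ratio at 120 min is exp(0.7 × exp(−120/240)) = exp(0.7 × 0.6065) = 1.53 and still falling, yet 39% to 77% are labelled optimal there. At τ = 30 the true ratio is 1.035 at 90 min and 1.013 at 120 min: those patients have essentially levelled off, so their 30% to 51% at T5 is mostly plateau and noise, not continuing improvement.

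**Step 3: dependence on the window.** With τ = 240 and s = 0.1, stopping at 60, 90 or 120 min puts 60%, 59% or 56% of patients at whichever reading is last. The most common optimum moves with the stopping time while the underlying course is unchanged.

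**Step 4: which tests are affected.** Everyone shares the same ceiling, so a rank method places all T5 values as tied top ranks. In simulated two-group data (25 per group, 40% and 50% at 120 min), the Gehan statistic with T5 treated as censored equalled the Mann-Whitney statistic on the raw times in every data set (maximum difference 0). Mean-based methods do not have this property. With assumed true optima that are lognormal (log-SD 0.5) and a V-shaped index around them, a true median of 120 min gives a true mean of 136 min against an assigned mean of 102. A true median of 150 min gives 170 against 110. At a true median of 60 min the gap is small, 68 against 65.

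**The case against.** The strongest reply is that the plan openly describes a 120-minute session, that the outcome can be read as the best of the scheduled times within it, and that boundary handling and choice of test usually belong in an analysis plan that is not shown here. Much of this stands. The choice of test is indeed left open, and the rank methods that deal properly with a common ceiling are already on the list. What does not fall away is the definition itself: it is fixed in this document, and followed exactly it gives 120 min to any patient still improving at T5.

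Three stronger readings are tempting and are not supported.

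- A reader might infer that the study expects steady improvement through 120 min, so most patients must hit the ceiling. No section says so. The Discussion attributes the benefit to the upright position and gives no time course; a quick change followed by a plateau, or a crossing below 1, fits the text equally well.
- A reader might infer that the comparison by surgical method and the bed-rest correlation are distorted whatever is done. As a censoring error, that holds for means, t-tests, ANOVA and Pearson, not for the listed rank alternatives.
- A reader might infer that every T5 value should be called not reached and analysed with Kaplan-Meier, log-rank or Cox. The closest-to-1 time is not an event time: a patient whose best reading is at 60 min might have come closer at 150 min. Some T5 values are also a true plateau or noise, as the 20% under a flat course shows.

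**Conclusion.** The point holds as a weakness in a stated rule: Definitions and Procedure together turn an optimum not yet reached into a recorded 120 min, in one primary and two secondary outcomes. Its size cannot be known from the protocol. On the assumed exponential course it ranges from near chance (about 20% to 32% at T5 for time constants of 5 to 15 min) to dominant (39% to 85% for 60 to 240 min). These shares depend wholly on the assumed starting ratio, time constant and noise, and they count plateau and noise as well as continuing improvement. If most optima lie well inside the window, little is lost. I would class it as a cheap improvement.

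**What to change.** Analysis wording only; the readings and the observation period stay as planned.

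1. In Definitions, describe the outcome as the best of the scheduled times within 120 min.
2. Report T5 values as 120 min or longer, with the number of patients there. This label does not claim that the optimum was missed in each of them.
3. With the mixed model already named, estimate the change from T4 to T5 in the distance of the index from 1, with its 95% confidence interval. If it still favours T5, state the conclusion as optimum not reached within 120 min.
4. For the comparison by surgical method and the correlation with bed rest time, specify Mann-Whitney, Kruskal-Wallis and Spearman in place of means, t-tests, ANOVA and Pearson. Kaplan-Meier or Cox is not needed.

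The cost is a few sentences, using the same data and methods already listed. The downside is that the headline may become at least 120 min and not a single number. No analysis can recover where an optimum beyond the last reading would have fallen.

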## Background

Post-operative pulmonary complications (PPCs), such as pneumonia, severe atelectasis, and respiratory failure, occur in about 10–50% of patients after a major upper abdominal surgery (1–3). Several factors contribute to the development of PPCs, including post-operative pathophysiological reductions in lung volumes, respiratory muscle function, mucociliary clearance, and pain inhibition of respiratory muscles (4). Following an upper abdominal surgery, PPCs are significantly associated with poor patient outcomes and result in an increased likelihood of rehospitalization, increased mortality and morbidity, longer hospital length of stay, and higher costs (5–10). Enhanced Recovery After Surgery (ERAS) Society Guidelines recommend early mobilization to improve recovery, reduce complication rates, and shorten inpatient hospital stays by reducing the physiologic derangement and stress response after surgery (11–14). While few studies have explored the method and duration for implementing mobilization, the indicators for measuring the effectiveness of post-operative early mobilization on pulmonary outcomes are lacking.

Electrical impedance tomography (EIT) is a non-invasive, radiation-free, bedside monitoring technique that provides dynamic images based on changes in the electrical conductivity of body sections through digital reconstruction (15). Within the chest, impedance can vary dynamically due to changes in lung volume (such as during respiration) and/or due to changes in blood and fluid content (such as within the heart during the cardiac cycle) (16). Thus, EIT can help evaluate the patient's ventilation distribution, which could lead to adjustments to the patient's early mobilization method and duration.

This study aims to evaluate the effect of post-operative early mobilization on lung ventilation function using EIT by assessing the ventilation distribution among various regions of interest (ROI) before and after mobilization in patients undergoing upper abdominal surgery. Additionally, the temporal differences in the distribution of ventilation in various regions of interest during mobilization will be explored to provide a theoretical basis for the development of personalized mobilization plans and precise treatment for patients after upper abdominal surgery.

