## Methods and Analysis

### Study Design

This prospective, single-center, single-cohort study will be conducted in the Surgical Intensive Care Unit (SICU) at the Liaocheng Cardiac Hospital in Shandong Province in China.

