## Discussion

The purpose of this study is to evaluate the effect of duration of post-operative early mobilization on the distribution of regional ventilation in patients undergoing upper abdominal surgery. Our study will involve the use of EIT that allows for the determination of changes in regional air content corresponding to different mobilization durations based on the changes in electrical impedance caused by inspired gas.

Following a major upper abdominal surgery, episodes of hypoxemia are common, as the restoration of a normal alveolar-to-arterial oxygen difference may take a few days. Functional residual capacity usually reaches its lowest value 1–2 days after surgery before slowly returning to normal values after 5–7 days post-operatively (20–22). Early mobilization prevents PPCs (23); improves pulmonary endurance, muscle strength, and quality of life (24–26); and also provides nursing staff an important measure to integrate the ERAS concept clinically (27). Sitting and standing during the first day after major abdominal surgery increase arterial oxygen saturation (28, 29). In fact, a significant reduction in PPC outcomes (odds ratio 0.08, 95% CI 0.010–0.71) was reported in patients who received enforced mobilization within 24 h after surgery for their gastrointestinal cancer (30). Also, patients undergoing abdominal surgery who were not mobilized (>10 min) within the first 24 h post-operatively were 3 times (95% CI 1.2–8.0) more likely to develop a PPC with each day out of surgery (31). Thus, early mobilization is clinically advised to decrease the risk of PPCs.

Atelectasis seen on CT scans during anesthesia persists for at least 24 h in most patients undergoing a major surgery. Based on a review of post-operative atelectasis in a heterogeneous group of non-thoracic patients, radiological evidence of atelectasis was found in 57% (539/944) of the patients up to 3 days post-operatively, with the diagnosis of atelectasis without radiography particularly challenging in the absence of fever (32). Thus, alternative methods monitoring post-operative lung function are essential to minimize the risk of PPCs (33). The effects of post-operative early mobilization on regional lung ventilation in patients undergoing an upper abdominal surgery have not been studied; EIT can be used clinically to fill this gap.

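### The optimal-duration primary outcome is the time of the best reading within one common sitting schedule, and cannot show that a session of that length is as good as a longer one

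*Protocol article*

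**What the plan says.** Under Outcome Measures: "The primary outcomes include the improvement in homogeneity of pulmonary ventilation distribution after mobilization and optimal duration of early mobilization". Under Definitions: "Optimal duration of early mobilization is defined as the mobilization time at which homogeneity index is closest to 1". Two secondary outcomes reuse the quantity: the optimum by surgical method, and its correlation with bed rest time.

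Study Design describes one cohort at one center. Under Procedure, each patient has a lying baseline (T0), is helped into a chair, and is read at 15, 30 and 60 min and then at "90 min (T_4_), and 120 min (T_5_) for each patient after getting out of the bed". The same section closes: "After patients reach the 120-min time point, their participation in the study will be complete", and adds that no further contact is planned.

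The Discussion opens: "The purpose of this study is to evaluate the effect of duration of post-operative early mobilization on the distribution of regional ventilation". The Abstract says that the temporal findings should help to develop personalized activity programs. Strengths and Limitations names the single center and the one-slice, body-position issue, and nothing about session length.

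**The concern.** To call a duration optimal is to say that stopping at that time is at least as good as going on. Evidence for that needs either sessions of different length to compare, or readings taken after sessions have ended. The schedule has neither. It gives a time course within one session, and the definition picks a point on it.

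The protocol's own rationale makes the gap matter. The Discussion attributes more uniform ventilation to the upright position and says that bed rest makes ventilation uneven. If the benefit is largely postural, some or all of it may be lost on return to bed. The moment at which the index is nearest 1 would then be a poor guide to how long a session should last.

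At stake is how one of the two primary results will be read. A best reading at, say, 30 min would be reported as an optimal duration of 30 min and could feed the personalized programs that the Abstract has in view. The same label would pass to the comparison by surgical method and the correlation with bed rest time.

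**Working it through.** The protocol gives no figure for this outcome to reproduce. Its sample-size statement (10 subjects needed, 50 planned) comes without an effect size or SD, and the point below would be the same at any sample size.

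**Step 1. What is observed**

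| Item | Protocol article | Section |
|---|---|---|
| Schedules given to patients | one, with readings to 120 min | Procedure |
| Values the outcome can take, as seated readings | five: 15, 30, 60, 90, 120 min | Procedure, Definitions |
| Session lengths assigned or compared | none | Study Design, Procedure |
| Readings after the session ends | none | Procedure |

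Let H(t) be the homogeneity index after t minutes of sitting. The design observes H(15), H(30), H(60), H(90) and H(120). The outcome is the t that minimizes |H(t) − 1|.

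**Step 2. What a statement about session length needs**

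Let G(u; s) be the index at time u for a patient whose session stopped at s, with u > s. Comparing a session of length s with a longer one requires G(u; s). No patient contributes a value of it, so no analysis of the planned data can recover it.

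**Step 3. Illustration (all values assumed)**

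A plateau would make the outcome depend on a tie, for which the definition has no rule, so I use a curve with a single best time.

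- Lying index: 1.8.
- Seated, t ≤ 30: H(t) = 1 + 0.8·exp(−t/15).
- Seated, t > 30: H(t) = H(30) + 0.001·(t − 30).
- Readings at 15, 30, 60, 90 and 120 min: 1.294, 1.108, 1.138, 1.168, 1.198. The defined optimum is 30 min.
- After stopping at s: G(u; s) = 1.8 − (1.8 − H(s))·exp(−(u − s)/τ).

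Mean |index − 1| over 6 h (minutes 0 to 360) by session length:

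| Assumption after the session | 15 | 30 | 60 | 90 | 120 | Smallest |
|---|---|---|---|---|---|---|
| Fades, τ = 30 min | 0.746 | 0.705 | 0.651 | 0.600 | 0.551 | 120 |
| Fades, τ = session length | 0.767 | 0.705 | 0.597 | 0.503 | 0.428 | 120 |
| Persists in full (τ infinite) | 0.304 | 0.129 | 0.155 | 0.179 | 0.200 | 30 |

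The five seated readings are identical in all three rows, yet the session length with the smallest mean deviation moves from 120 to 30 min. The answer turns on the part of the curve that is not measured. The table says nothing about which length is clinically right.

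**The case against.** The strongest reply is that the protocol defines its term openly and that its aim is about what happens while the patient is up. The Abstract and Background speak of temporal differences during mobilization, and the Background calls them exploratory and a theoretical basis. On this view, asking about benefit after the session replaces the protocol's question with another. Part of this stands: as a description of the in-session course, the outcome is legitimate and the data collection is sound. But optimal is a word of evaluation, the Discussion states the purpose as the effect of duration, the Abstract points to activity programs, and the limitations are silent.

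Three stronger readings are tempting, and the documents do not support them.

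- A reader might infer that the shorter durations are never observed at all. By schedule, every patient sits for 15, 30, 60 and 90 min and is read at each time, and each reading shows the state at the end of that much sitting. What is missing is what follows, and any contrast between lengths.
- A reader might take the Background clause "which could lead to adjustments to the patient's early mobilization method and duration" as a claim that this study compares methods. In context it describes a possible use of EIT.
- A reader might hold the Discussion phrase "determination of changes in regional air content corresponding to different mobilization durations" to be false. It can fairly describe readings at different elapsed times, and that section never uses the term optimal duration.

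**Conclusion.** The point holds as a mismatch between a label and a design. The second primary outcome is the elapsed time at which ventilation is most even during a session observed to 120 min. It cannot show that a session of that length is as good as or better than a longer one. One of two primary outcomes and two secondary outcomes are affected; the improvement in homogeneity is not. The mismatch should be corrected, but it does not invalidate the data collection.

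The conclusion rests on reading Procedure to mean that patients stay seated through the 120-min reading. If some return to bed sooner, elapsed time represents session length even less well. The size of the error cannot be given, because the documents say nothing about how the index behaves after sitting ends. The illustration shows only that the ranking of session lengths can go either way.

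**What to change.** - **Outcome Measures and Definitions:** rename the second primary outcome, and the two secondary outcomes built on it, *time to most even ventilation (homogeneity index closest to 1) during a chair-sitting session observed to 120 min*.
- **Discussion, first sentence:** state the purpose as describing the time course of ventilation distribution during mobilization, in place of the effect of its duration.
- **Strengths and Limitations:** add that sessions of different length were not compared and no post-session readings were taken, so the study cannot recommend a session duration.

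The Background clause on method and duration needs no edit.

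The cost is a less ambitious stated claim. Schedule, measurements, sample size and clinical procedure stay as they are.
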